##### 8.1.4.2 Storage after dilution

Diluted solution should be used immediately. If not used immediately, the solution may be stored in a refrigerator at 2-8°C for up to 24 h.

All temperature excursions outside of 2-8°C have to be documented. To report temperature deviations (during shipment and storage at the site), the product quality complaint form has to be completed by the site and forwarded to [REDACTED] immediately. The IMP needs to be put into quarantine until notification by the sponsor. For further details, please see the information on drug supply, handling and IMP deviations guideline.

## 8.2 Administration of experimental and control interventions

### 8.2.1 Experimental Intervention

Talineuren will be dispensed to the patient by health care professionals at the defined time points according to protocol. Blank spaces of the label (on box and vial) need to be filled in before the medication is dispensed to the patient. The experimental treatment consists of TLN and it will be administered once weekly as an intravenous infusion up to 14 weeks or until unacceptable toxicity (part 1) and up to 8 weeks or until unacceptable toxicity (part 2) or other reasons listed under section **8.3 Dose modifications**.

#### 8.2.1.1 Dilution

Talineuren must never be administered undiluted. Before administration, TLN must be diluted with saline solution 0.9%. All planned doses are diluted by mixing the required dose of TLN (60 mg per 10 ml) in a 500 ml sterile bag pre-loaded with 250 ml of 0.9% saline solution.

#### 8.2.1.2 Administration

After dilution, TLN is administered as intravenous infusion. In case of extravasation, infusion must immediately be stopped and restarted using a different vein. It is recommended to apply cold packs to

mitigate local irritation. In case of skin contact due to spilling or efflux of TLN solution from the infusion insertion site, rinse with water.

Administration speed is 250 ml/h using an infusion pump. During infusion, the solution should be protected from direct sunlight.

8.2.2 Control Intervention Experimental Intervention  
Not applicable.

### 8.3 Dose modifications

Dose modifications are foreseen in cases where a causal relationship to the treatment with TLN cannot be excluded. A causal relationship in this trial is defined as a possible, probable or definite linkage to TLN according to ICH E2A (for more details see section **10. Safety**).

Any grade 4 event with causal relationship to treatment is judged as unacceptable toxicity and will lead to a stop of treatment without resuming the treatment in the affected patient.

Any SAE leads to a treatment stop for the affected patient with the following exception:

- if there is no causal relationship to TLN and the definition for an SAE is fulfilled **uniquely due to an overnight hospital stay (1 night) for an otherwise not severe or serious medical problem**, the patient can continue study participation.

In case of an SAE with no causal relationship to TLN, the patient will be replaced.

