#### 6.1.1 Dose escalation (Part 1)

In this part a group of 3 patients will receive a single weekly dose that will be increased according to the schedule defined. In parallel, meaning that the first patient will receive a dose X on week Y, if the safety assessment is positive (see **Section 8.3 Dose modifications**) then the following week (Y+1) this patient will receive the next dose (X+1), on that week (Y+1) two other patients will receive the same dose X to confirm the safety assessment. *In fine*, every week patient 1 will receive one dose at the same time that patients 2 & 3 receive the preceding dose.

This weekly increase has been elected to allow rapid determination of the MSD and rapidly reach a dose level that will be beneficial for the patients involved in this trial. This is allowed by the fact that GM1 is expected to be safe and no clear AE are foreseen within this dose range. Furthermore, the 1 + 2 pattern allows one week observation of each dose increase in 1 patient before infusing 2 more.

The first dose level starts at 6 mg which will increase to 12 and 60 mg, then increasing by equal steps of 60 mg up to 720 mg. The escalation will be stopped individually according to the decision matrix detailed in the **Section 8.3 Doses modifications**. The three first steps of the dose are purposely low to account for any possible unexpected effects of the formulation.

Throughout the escalation part, all patients will be monitored twice weekly to record AEs and document them. Monitoring will take place once before each TLN infusion (beginning of the week) and a second time by the end of each week (performed by the principal investigator) to collect AE and allow enough time for the IMC to review them and take their decision on the next infusion/dose modification/delay.

At the end of the escalation, the average of the three maximum tolerated doses by the three patients will be defined as MSD for part 2. With this design, we aim to find the highest dose that generates, if any at all, at maximum only transient mild/moderate AEs. At the same time, this will allow to glean information on clinical effect for the planning of a potential phase II study.

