#### Part 1 – Dose escalation:

| Causality            | Intensity   | Resolution until next infusion | Next patient added/ Dose increase                                                                                                         |
|----------------------|-------------|--------------------------------|-------------------------------------------------------------------------------------------------------------------------------------------|
| (unlikely/unrelated) | grade 1 - 3 | yes/no                         | yes                                                                                                                                       |
| Possible             | grade 1     | yes                            | yes                                                                                                                                       |
| Possible             | grade 1     | no                             | yes                                                                                                                                       |
| Possible             | grade 2     | yes                            | yes                                                                                                                                       |
| Possible             | grade 2     | no                             | Delay till resolution (maximum of 3 weeks), then rechallenge at same dose level, if re-occurrence stop treatment for the affected patient |
| Possible             | grade 3     | yes/no                         | no (stop treatment for the affected patient but others to continue)                                                                       |
| Probable/definite    | grade 1     | yes/no                         | yes                                                                                                                                       |
| Probable/definite    | grade 2     | yes                            | yes                                                                                                                                       |
| Probable/definite    | grade 2     | no                             | no (stop treatment for the affected patient but others to continue)                                                                       |

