| Probable/definite    | grade 3     | yes                            | stop (for the affected patient but others to continue)                                                                                    |
| Probable/definite    | grade 3     | no                             | Stop for all patients                                                                                                                     |

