#### Assessment of Intensity

| Grade | Type             | Description                                                                                                                                                                    |
|-------|------------------|--------------------------------------------------------------------------------------------------------------------------------------------------------------------------------|
| 1     | mild             | Awareness of a sign or symptom that does not interfere with the trial participant's usual activity or is transient, resolved without treatment and with no sequelae            |
| 2     | moderate         | Interferes with the trial participant's usual activity and/or requires symptomatic treatment.                                                                                  |
| 3     | severe           | Medically significant, but not life-threatening. Symptom(s) causing severe discomfort and significant impact of the trial participant's usual activity and requires treatment. |
| 4     | Life-threatening | Emergency intervention needed.                                                                                                                                                 |
| 5     | lethal           | Death due to SAE.                                                                                                                                                              |

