### 11.3 Statistical criteria of termination of trial

There are no statistical stopping rules for this trial. Guidance regarding the discontinuation of the trial subjects, cohorts or the entire trial based on reported AEs are provided in chapter 8.3 **Dose modifications**.

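### Section 8.3 stops all Part 1 patients for an unresolved severe event, but names only the affected patient for a related life-threatening, fatal or serious one

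*Protocol*

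**What the plan says.** Section 11.3 states that the trial has no statistical stopping rules and continues: "Guidance regarding the discontinuation of the trial subjects, cohorts or the entire trial based on reported AEs are provided in chapter 8.3". Section 8.3 is thus where the protocol itself places the rule for stopping more than one patient.

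Section 8.3 has general sentences and a decision matrix for each part.

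- **Related grade 4 event.** It counts as unacceptable toxicity and "will lead to a stop of treatment without resuming the treatment in the affected patient". Related means possible, probable or definite.
- **SAE.** "Any SAE leads to a treatment stop for the affected patient", with one exception for an unrelated event that is serious only because of a single night in hospital.
- **Part 1 matrix.** Two entries read "no (stop treatment for the affected patient but others to continue" and one reads "stop (for the affected patient but others to continue" (closing brackets omitted). A probable or definite grade 3 event not resolved by the next infusion carries "Stop for all patients".

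The intensity scale in section 10.1 goes up to grade 5, described as "Death due to SAE". Section 8.3 does not mention grade 5.

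Under section 6.1.1, patient 1 goes first at each level. One week later, as patient 1 moves to the next dose, "two other patients will receive the same dose X to confirm the safety assessment".

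**The concern.** A stopping scheme should not react less widely as events get worse. Here the widest written reaction belongs to a grade 3 outcome, while the next two grades up carry a written consequence for one patient only.

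The patients affected are the other two in Part 1. If patient 1 has a related life-threatening reaction at a dose, patients 2 and 3 are due that same dose the following week. If patient 2 or 3 has it, patient 1 is already one level higher and due to go up again. Section 3.7 names first human use of the infusion as the main risk for escalation patients, and section 3.3.4 says no GLP toxicity study was done with the liposomal product itself. A rule for this situation is best fixed before it arises.

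**Working it through.** The protocol gives no figure on this point, so the check sets the rules side by side.

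**Step 1: count the Part 1 matrix (section 8.3).**

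- Dose increase allowed, 6 rows: unlikely/unrelated grade 1–3; possible grade 1 resolved; possible grade 1 unresolved; possible grade 2 resolved; probable/definite grade 1; probable/definite grade 2 resolved.
- Delay and rechallenge, then stop the affected patient on recurrence, 1 row: possible grade 2 unresolved.
- Stop the affected patient while the others go on, 3 rows: possible grade 3; probable/definite grade 2 unresolved; probable/definite grade 3 resolved.
- Stop everyone, 1 row: probable/definite grade 3 unresolved.

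Total: 6 + 1 + 3 + 1 = 11 rows. Rows for grade 4 or 5: 0.

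**Step 2: order the written consequences by severity.**

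| Event in one Part 1 patient | Affected patient | Other Part 1 patients |
|---|---|---|
| Possible grade 3 | stop | told to continue |
| Probable/definite grade 3, resolved | stop | told to continue |
| Probable/definite grade 3, unresolved | stop | stop |
| Related grade 4 | stop, no resumption | nothing written |
| Related grade 5 | covered only by the SAE sentence | nothing written |
| Related SAE | stop | nothing written on account of seriousness |

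The reach of the rule widens to all patients at row three and narrows again from row four. One qualification applies to the last row: a related SAE that is also an unresolved probable/definite grade 3 event does stop everyone, but through its grade, not because it is serious.

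**Step 3: look for a rule elsewhere in the protocol.**

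- 1.6: the IMC meets weekly in principle and must agree unanimously for each patient to go on. No criterion is given.
- 1.7: the DSMB is advisory. Its scheduled Part 1 meetings follow levels 5, 10 and 15; no event-triggered meeting is stated.
- 2.9: the sponsor may terminate, with participant safety as one example. It is an option, not a trigger.
- 6.1.1: progression depends on a positive safety assessment, defined by reference back to 8.3.
- 7.3: unacceptable toxicity withdraws the patient concerned.
- 8.1.1: escalation runs until unacceptable toxicity, again by reference to 8.3.
- 10.1.1: SAEs reach the sponsor within 24 hours. This is reporting, not a dosing rule.

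None of these says what happens to the other two patients after a related grade 4 or 5 event or a related SAE.

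**The case against.** The best defence is that no patient is dosed by default. The IMC includes an external physician and decides unanimously, so one objection is enough to hold a patient. Section 6.1.1 adds twice-weekly adverse event monitoring, timed so that the IMC can act before the next infusion, and makes progression conditional on a positive assessment. A related life-threatening or fatal event in patient 1 could hardly be called positive. The DSMB charter and the safety management plan are not shown and may say more.

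Much of this stands. These safeguards make it unlikely that the other patients would simply be infused the next week. They do not remove the gap: the 6.1.1 gate takes its meaning from 8.3, which is silent here, and the IMC is given no criterion. Nor does the gate, as written, address patient 1 after an event in patient 2 or 3.

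Three stronger readings should be resisted.

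- A reader might infer that the protocol orders the others to continue after a grade 4 event. It does not. That instruction appears only in the three matrix rows listed above; for grade 4 and for SAEs as such the text is silent.
- A reader might infer that nothing but unguided discretion protects the other two patients. The required unanimous decision is a real gate.
- A reader might infer that a rule is also missing for the case where patients 2 and 3 both stop at a dose patient 1 has passed, and that the maximal suitable dose could then be set too high. Section 6.1.1 chooses individual stopping, and the matrix expressly lets others continue after lesser events, so a rule counting stops across patients would be a different design. Any effect on the maximal suitable dose would come from averaging three maxima, a separate matter, and 1.7 schedules a DSMB meeting once that dose is set.

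**Conclusion.** The point holds as an inversion in the written Part 1 rules. The section that 11.3 designates for cohort and trial stopping contains one all-patient trigger in Part 1, an unresolved probable/definite grade 3 event. It provides none for related grade 4 events, related deaths or related SAEs as such. No numerical effect is claimed: the size of the gap is which events lack a rule, and the patients exposed are the other two of three.

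The conclusion rests on the protocol text alone and assumes that no unseen document supplies the missing rule. If the DSMB charter or the safety management plan does, 8.3 should still state it or point to it, because 11.3 sends the reader to 8.3. The matter should be corrected. It does not undermine the design of individual escalation.

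**What to change.** Add one rule to section 8.3, Part 1: a grade 4 or 5 event, or an SAE, judged possibly, probably or definitely related to the product in any Part 1 patient pauses dosing and escalation for all Part 1 patients until an IMC review, with DSMB advice, has been documented. State that the rule takes precedence over the matrix where both apply, since a related SAE of grade 3 can otherwise fall in a row that lets the others go on. The existing all-patient stop and the individual rules for non-serious events of grade 1 to 3 stay as they are.

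Leave the three-week delay limit in section 7.3 unchanged. It bounds the pause: if the review takes longer, the patients concerned are withdrawn under the rule already in force.

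The cost is a short protocol amendment and a review outside the DSMB's scheduled meetings when the rule is triggered. The downside is that escalation may be delayed or end earlier. In exchange, the decision on the other two patients is made under a rule set in advance.

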#### Part 1 – Dose escalation:

| Causality            | Intensity   | Resolution until next infusion | Next patient added/ Dose increase                                                                                                         |
|----------------------|-------------|--------------------------------|-------------------------------------------------------------------------------------------------------------------------------------------|
| (unlikely/unrelated) | grade 1 - 3 | yes/no                         | yes                                                                                                                                       |
| Possible             | grade 1     | yes                            | yes                                                                                                                                       |
| Possible             | grade 1     | no                             | yes                                                                                                                                       |
| Possible             | grade 2     | yes                            | yes                                                                                                                                       |
| Possible             | grade 2     | no                             | Delay till resolution (maximum of 3 weeks), then rechallenge at same dose level, if re-occurrence stop treatment for the affected patient |
| Possible             | grade 3     | yes/no                         | no (stop treatment for the affected patient but others to continue)                                                                       |
| Probable/definite    | grade 1     | yes/no                         | yes                                                                                                                                       |
| Probable/definite    | grade 2     | yes                            | yes                                                                                                                                       |
| Probable/definite    | grade 2     | no                             | no (stop treatment for the affected patient but others to continue)                                                                       |
| Probable/definite    | grade 3     | yes                            | stop (for the affected patient but others to continue)                                                                                    |
| Probable/definite    | grade 3     | no                             | Stop for all patients                                                                                                                     |

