If a patient drops out for reasons unrelated to the drug treatment, this patient will be replaced. The three MSD are necessary to establish the dose that will be used for the multiple dose administration. This is a design that allows fast escalation with minimal risks for the patients since the dose steps are small, the starting dose is very low and each increment is split in a 1 + 2 pattern. With N=3 we expect to show evidence of common AEs inherent to the TLN formulation. This design (part 1) lacks the assessment of mid-term cumulative effects of the drug at a constant dosage. Therefore, an additional phase (part 2) will be performed to complete the safety profile under constant weekly dosages and provide more insight of the tolerability over 8 repeated doses.

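### When lead patient 1 is stopped in Part 1, Section 8.3 lets the others continue without saying at which dose level or behind which lead, which conflicts with the 1 + 2 rule in Section 6.1.1

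*Protocol*

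**What the plan says.** Section 6.1.1 sets up a staggered escalation. Patient 1 receives dose X. If the safety assessment under Section 8.3 is favourable, patient 1 moves up a level the following week and patients 2 and 3 receive X. The protocol relies on this order as a protection: "the 1 + 2 pattern allows one week observation of each dose increase in 1 patient before infusing 2 more". It repeats, with no exception, that "each increment is split in a 1 + 2 pattern". The same section says "The escalation will be stopped individually according to the decision matrix". It also sets the maximal suitable dose (MSD) for Part 2 as the mean of the three patients' own maximum tolerated doses. A patient who leaves for reasons not linked to the drug is replaced.

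Section 8.3 supplies the decision table for Part 1. Its action column is headed "Next patient added/ Dose increase". The relevant rows are:

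- Possible grade 3, and unresolved probable/definite grade 2: "no (stop treatment for the affected patient but others to continue".
- Resolved probable/definite grade 3: "stop (for the affected patient but others to continue".
- Unresolved probable/definite grade 3: "Stop for all patients". This is the only row that stops everyone.
- Unresolved possible grade 2: delay for up to three weeks, then rechallenge at the same level. The other patients are not mentioned.

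The text above the table stops a patient for any related grade 4 event, and it too is silent on the other patients. The summary of the Part 1 schedule, placed after Section 8.9 and before the visit tables, has all three patients start at 6 mg, ideally together, with each moving up on his or her own criteria. It describes no stagger.

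**The concern.** The 1 + 2 order works only while there is a patient ahead. Section 8.3 defines the events that remove a patient, and it gives the same instruction whether that patient is the lead or a follower. If a follower is stopped, letting the others continue does no harm to the order. If patient 1 is stopped, the instruction meets the condition in Section 6.1.1 that patients 2 and 3 receive a dose only after patient 1 has done well on it. The protocol does not say which of the two governs.

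Two things are at stake. The first is exposure in a trial that gives this formulation intravenously to humans for the first time: new levels could be opened in two patients in the same week. The second is the dose given to the nine Part 2 patients, because the MSD is the mean of three personal maxima and two of them depend on how far patients 2 and 3 are taken.

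**Working it through.** The protocol gives no figure to reproduce here. The check sets the rules side by side and then works out what they imply for the MSD.

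**Step 1: patient 1 is stopped at dose X.** In that week patients 2 and 3 have received the level below X.

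- Section 6.1.1: X goes to patients 2 and 3 only after a favourable assessment of patient 1 at X. There has been none.
- Section 8.3: the other patients continue. No level is given.
- Replacement: Section 6.1.1 covers drop-out for reasons not linked to the drug, and Section 8.3 covers unrelated serious events. Section 8.3 counts possible, probable and definite as causally related, so a lead stopped under any of the three rows falls outside both rules. No new lead is named.
- Result: if patients 2 and 3 escalate, both receive each later level in the same week and nobody is a week ahead.

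**Step 2: patient 1 is delayed.** Patient 1 received X in week Y and is held for the maximum three weeks, from Y+1 to Y+4. If the others kept to the weekly schedule they would receive X, X+1, X+2 and X+3 in weeks Y+1 to Y+4. They would pass patient 1 in week Y+2 and be three levels ahead at the rechallenge. This requires the favourable-assessment condition to be set aside. The delay row neither says so nor says that the others wait.

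**Step 3: effect on the MSD.** Inputs: the dose ladder in Section 8.1.1 (6, 12, 60 mg, then steps of 60 mg to 720 mg at level 14) and the averaging rule in Section 6.1.1. Let patient 1 be stopped at level k, so that the last tolerated dose of all three is d(k−1).

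- Lower bound, others go no further: MSD = d(k−1).
- Upper bound, both others reach 720 mg with no event: MSD = (d(k−1) + 720 + 720)/3.

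| Patient 1 stopped at | Lower bound | Upper bound |
|---|---|---|
| Level 4 (120 mg) | 60 mg | (60 + 1440)/3 = 500 mg |
| Level 6 (240 mg) | 180 mg | (180 + 1440)/3 = 540 mg |
| Level 8 (360 mg) | 300 mg | (300 + 1440)/3 = 580 mg |
| Level 12 (600 mg) | 540 mg | (540 + 1440)/3 = 660 mg |

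An intermediate case for level 6: if both followers end with 420 mg as their last tolerated dose, MSD = (180 + 420 + 420)/3 = 340 mg.

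Section 9.2.2 words the rule as the mean of the doses reached. On that wording the level 6 bounds are (240 + 180 + 180)/3 = 200 mg and (240 + 720 + 720)/3 = 560 mg, so the picture is the same.

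In the upper-bound case at level 6, levels 7 to 14 (8 of 14) are given to two patients together with no lead.

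**Step 4: opening a level in two patients instead of one.** The protocol gives no event risk, so a per-patient risk p is assumed. The chance of at least one event in the week a level is first given is p with one patient and 1 − (1 − p)² with two: 5.0% against 9.8% at p = 5%, 10% against 19% at p = 10%, and 30% against 51% at p = 30%.

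**The case against.** A reader might infer that the site cannot tell whether patients 2 and 3 go on at all, because the cell opens with a refusal under a heading that asks about adding the next patient. The protocol does not support that. The cell itself says the others continue, Section 6.1.1 stops escalation patient by patient, and a mean of three personal maxima presupposes that patients can stop at different levels. The Part 2 table uses the identical wording under a heading about repeating the dose, where no patient is being added, so the refusal can be read as concerning the affected patient's own infusion. This stands. What is missing is the level and the lead. On that reading, moreover, the half of the Part 1 heading about adding the next patient gets no answer beyond the general instruction to continue.

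Oversight also counts. The IMC (Section 1.6) meets weekly in principle and must agree unanimously for each patient, with an independent external physician among its three members, so escalation without a lead would not happen automatically. The Data Safety Monitoring Board also meets after levels 5 and 10. This softens the problem, but neither section gives a rule for a lost or delayed lead, and the IMC would have two conflicting sections to apply.

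The 1 + 2 order is not the only protection. Section 6.1.1 also cites small steps, a very low starting dose, the expected safety of GM1 and twice-weekly monitoring. That is fair, but the order is the only one of these that gives a week's warning at each new level.

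On the delay row, an unresolved event in patient 1 is hard to call a favourable assessment, so the natural reading may be that the others wait. That too is fair: the overtaking in Step 2 is what the silence permits, not what the protocol instructs.

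**Conclusion.** The conflict is real and specific. In three rows Section 8.3 lets the others continue after a patient is stopped. When that patient is the lead, this cannot be squared with Section 6.1.1, and nothing states the level, the new lead or a replacement. The delay row leaves the same question open, and the Part 1 schedule summary contradicts the stagger from the first dose.

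For a stop at level 6 the MSD could lie anywhere from 180 to 540 mg. A reader might take the threefold ratio as the expected effect. It is not. The lower end holds the others where they are, which sets aside the instruction that they continue. The upper end assumes that neither has any limiting event up to 720 mg and that the IMC approves every step. The range narrows as patient 1 is stopped later. The finding itself rests on the wording of the sections and on no assumed event rate.

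**What to change.** Split the action column of the Part 1 table in Section 8.3 into two: one for the affected patient's next infusion, and one for what the other patients may receive, at the same level and at higher levels. Apply the same split to the delay row and to the related grade 4 rule above the table. Add a sentence saying what happens to the 1 + 2 order when patient 1 is stopped or delayed. Bring Section 6.1.1, Section 8.3 and the Part 1 schedule summary into agreement on whether the three patients start together or staggered. Which passage prevails is for the sponsor and the IMC to decide; no clinical rule is proposed here.

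The cost is one table, one sentence and a correction to the schedule summary. The downside is that escalation may take some weeks longer if patient 1 is stopped or delayed.
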